### Ethics approval and consent to participate

Our research is conducted in accordance with the principles of the Declaration of Helsinki (64th WMA General Assembly, October 2013) and was approved by the Ethics Committee of First Affiliated Hospital of Shandong First Medical University. Written informed consent will be obtained from all participants and/or their legal representatives. The results will be disseminated through a peer-reviewed publication and in conferences or congresses.

## Discussion

Older adults with frailty are becoming more prevalent as a result of the rapidly aging population [36,37], which in turn puts more strain on the world’s healthcare systems [38]. Older adults with frailty are more likely to experience unmet care needs, fractures and falls, hospitalizations, iatrogenic consequences, and early mortality [14,39–43]. Surgical patients who are geriatric are more likely to experience "age-related events," mainly respiratory complications (pneumonia and respiratory failure), heart problems, postoperative cognitive impairment, an increased likelihood of ICU admission, an extended hospital stay, and higher mortality [44].

Consequently, strategies that target the prevention and management of frailty in an ageing population will probably reduce the burden that the condition imposes on both the individual and health systems. It is recognized that frailty is a clinical syndrome related to aging [45–47] that it is often characterized by a decline in many organ systems’ physiological capacity [14,42,47,48], making them more susceptible to stress [14,42,43,45–47]. The functional capacity of a fragile person rapidly diminishes when stressor events occur (such as an acute illness). In order to prevent or reduce frailty from progressing into significant functional impairments, health care policy and supply must implement interventions to prevent or reduce frailty. One of the most typical clinical consequences in geriatric patients is POD [2,3,18]. Its incidence is also directly tied to a number of severe postoperative complications, and the two together are linked to extremely detrimental outcomes. In order to improve perioperative management through early preoperative identification of frail patients, an examination of the impact of preoperative frailty on delirium in geriatric patients undergoing noncardiac surgery is the purpose of this study. This will help prevent or reduce the occurrence of POD and a number of serious consequences.

According to the inclusion and exclusion criteria, patients will undergo a rigorous screening process. Researchers who have been trained and evaluated will do the preoperative and postoperative follow-up and data collecting for the chosen patients. This research is based on observation. The conclusions will reflect the significance of preoperative frailty assessment and further demonstrate which frailty index indicators are independent risk factors related to POD from the findings of multivariate regression analysis. In geriatric patients undergoing noncardiac surgery, this will serve as a basis for preventing POD.

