### Sample size calculation

The main outcome will be the incidence of POD. Based on literature review and early study results, the estimated incidence of frailty in surgical patients was 23.0%, while the incidence of POD in the frailty and nonfrailty groups was 35.7% and21.7%. PASS 15.0 software was used to determine the sample size for the independent sample rate comparison of the two groups. The ratio of samples between the experimental and control groups was 0.303, and the two-sided test. Test level (α), and inspection effectiveness (1-β) were set at 0.05 and 0.80, respectively. This calculation yielded a sample size of 112 patients in the frailty group and 370 patients in the nonfrailty group. Considering 10% dropout rate, a total of 536 study volunteers will be required, consisting of 411 patients in the nonfailty group and 125 patients in the failty group.

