### Study implementation

All members of the research team will receive systematic training to master and use the MMSE, aCCI, mFI, BI, 3D-CAM, and CAM-ICU before the study and may only participate after passing the examination.

**Preoperative frailty assessment:** The mFI is a National Surgical Quality Improvement Gauge (NSQIP)-based 11-factor index that has been proven to adequately reflect frailty and predict mortality and morbidity [32]. The mFI is calculated by dividing the number of factors present for a patient by the number of available factors for which there are no missing data [33]. An mFI score of 0 is classified as healthy, 0–0.21 is classified as a prefrail, and ≥ 0.21 is classified as a prefrail. The index includes 11 items: nonindependent function or activity status; history of diabetes; history of chronic obstructive pulmonary disease (COPD) or pneumonia; history of congestive heart failure; history of myocardial infarction; angina pectoris, percutaneous coronary intervention (PCI), cardiac surgery; hypertension requiring medication; peripheral vascular disease or static pain; sensory disturbance; transient ischaemic attack (TIA) attack or cerebrovascular accident without sequelae; cerebrovascular accident with sequelae [34]. In this study, patients with moderate and severe dysfunction with a BI ≤ 60 are considered to be positive for item 1. The advantage is that it has been employed and is frequently used in the risk classification of various surgical operations in the NSQIP database of the United States.The majority of evaluation indexes are comorbidities, poor nutrition, metabolism, and other physical function indexes, which is a drawback.**Assessment of activities of daily living:** The patients will be assessed preoperatively by the BI evaluation form; 0–40 is classified as severe dysfunction, 41–60 is classified as moderate dysfunction, 61–99 is classified as mild dysfunction, and 100 is classified as self-care.**Diagnosis of POD:** The 3D-CAM will be used to evaluate POD twice a day (8:00–10:00 and 18:00–20:00) on the the 1^st^ to 7^th^ postoperative days. The 3D-CAM provides a brief assessment (3 orientation items, 4 attention items, 3 symptom probes, and 10 observational items) that facilitates rating of the 4 core CAM features and has a sensitivity of 95% and specificity of 94% when compared with a clinical reference standard rating in a prospective validation study in hospitalized patients [35].

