### Statistical methods

Continuous variables will be subjected to normality tests (such as age). If the data have a normal distribution, the mean ± standard deviation will be used to represent the data. Intergroup comparisons will be made using independent-sample t tests. In the absence of a normal distribution, medians (interquartile range) will be used to express the data, and the Wilcoxon rank sum test will be applied to compare the groups. A categorical variable, such as the sex or complications, will be expressed as a frequency (percentage). We will use either the chi-square test or Fisher’s exact probability approach for intergroup comparisons.

The primary outcomes of POD will be analyzed using a logistic regression model. The correlation between weakness and POD will be calculated using odds ratios (ORs) and 95% confidence intervals (CIs).

Kaplan-Meier survival curves will be used to describe the incidence of secondary outcomes. We will use the log-rank test to compare the differences between groups. A Cox regression model will be used to analyze the influencing factors for 30-day readmissions and complications.

In order to compare the abscission rate between the two groups, the chi-square test will be used.

All statistical analyses will be conducted using the two-sided test with a p value < 0.05 considered statistically significant.

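### The Discussion promises to demonstrate which of the 11 mFI items are independent POD risk factors, but the plan supports only an exploratory item-level analysis

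*Protocol article*

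**What the plan says.** - **Discussion:** the conclusions will "further demonstrate which frailty index indicators are independent risk factors related to POD from the findings of multivariate regression analysis". The paragraph then says that, for this patient group, "this will serve as a basis for preventing POD".
- **Study implementation, preoperative frailty assessment:** "The index includes 11 items", and the list that follows does count to 11.
- **Statistical methods:** "All statistical analyses will be conducted using the two-sided test with a p value < 0.05 considered statistically significant". The section gives no multiplicity rule. On POD it says "The primary outcomes of POD will be analyzed using a logistic regression model", and the association it goes on to describe is that between frailty and POD. No item-level model is described, and nothing is labelled exploratory.
- **Sample size calculation:** the study is sized for one comparison of two proportions, where "the incidence of POD in the frailty and nonfrailty groups was 35.7% and21.7" percent respectively.

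**The concern.** The Discussion sentence says what the study will conclude. Read with the blanket threshold in Statistical methods, it allows any mFI item with p < 0.05 to be reported as an independent risk factor. That is a family of up to 11 tests with no error control, in a study sized for a single contrast.

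Two features make attribution to single items fragile. Some items are neighbours by definition: myocardial infarction sits beside angina, PCI or cardiac surgery, and cerebrovascular events without sequelae sit beside those with sequelae. Uncommon items will also have little power, so a non-significant item may be misread as harmless, and an uncommon item that does reach significance will tend to have an exaggerated OR.

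At stake is whether a comorbidity is named as a target for preventing POD when the finding is due to chance. The main frailty result is not at stake.

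**Working it through.** **1. The plan's own sample size.** Inputs from Sample size calculation: POD 35.7% and 21.7%, frail-to-nonfrail ratio 0.303, two-sided alpha 0.05, power 0.80.
- Pooled proportion: (0.303 × 0.357 + 0.217)/1.303 = 0.2496.
- Frail n without continuity correction: [1.96·√(1.303 × 0.2496 × 0.7504) + 0.8416·√(0.357 × 0.643 + 0.303 × 0.217 × 0.783)]² / 0.14² = 102.1, so 103 frail and 340 nonfrail.
- With continuity correction: (102.1/4)·[1 + √(1 + 2 × 1.303/(102.1 × 0.14))]² = 111.2, so 112 frail and 112/0.303 → 370 nonfrail. This matches the plan.
- Dropout: 482/0.9 → 536, which also matches.

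The stated size is thus fully accounted for by the single frail versus nonfrail contrast.

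**2. Expected events.** 112 × 0.357 + 370 × 0.217 = 40.0 + 80.3 = 120.3 POD cases in 482 patients (25%), or 120.3/11 = 10.9 per item before any confounder is added.

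**3. Chance of at least one false item at unadjusted 0.05.** For k null items and independent tests this is 1 − 0.95^k.

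| Scenario | Chance of ≥ 1 false item |
|---|---|
| All 11 null, independent | 43.1% |
| All 11 null, test correlation 0.1 / 0.2 / 0.3 / 0.5 | 42% / 40% / 37% / 30% |
| 8 null items, independent | 33.7% |
| 5 null items, independent | 22.6% |
| Simulated 11-item logistic model, n = 482, 25% POD, all null | 39–40% |

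The correlated rows are simulations with equal correlation between all test statistics. The last row uses assumed item prevalences between 5% and 50%. The expected number of false items if all 11 are null is 11 × 0.05 = 0.55.

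**4. Power and exaggeration for single items.** The article gives no item prevalences, so those below are assumptions. Method: n = 482, overall POD 25%, single-item Wald test. SE(log OR) = √(1/[n·q·p1(1−p1)] + 1/[n(1−q)·p0(1−p0)]), where q is item prevalence and p1 and p0 are the POD risks with and without the item. Power = Φ(log OR/SE − 1.96).

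| Assumed prevalence | SE for OR 2 | Power, OR 2, p < 0.05 | Power, OR 2, p < 0.05/11 |
|---|---|---|---|
| 5% | 0.432 | 36% | 11% |
| 10% | 0.317 | 59% | 26% |
| 30% | 0.220 | 88% | 62% |
| 50% | 0.216 | 89% | 64% |

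For a true OR of 1.5, the average among results significant in the right direction is about 3.0 at 5% prevalence (power 15%) and about 1.8 at 50%. Correlation between items in a joint model would lower power somewhat.

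**The case against.** Several objections are fair, and most of them limit the point.

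- **The 43% is a worst case.** It needs all 11 items null and independent tests. The plan assumes POD of 35.7% versus 21.7% by mFI group, an OR of (0.357/0.643)/(0.217/0.783) = 2.0, and the mFI is the number of these items present divided by the number available. If that assumption is right, some items very probably carry signal. The overlap between items also undercuts independence. This stands, and is why a range is given.
- **No item-level analysis is specified.** The claim is one forward-looking sentence in the Discussion, and an article may leave the model and its multiplicity handling to a full protocol or SAP that is not shown. This stands in part: the absence of a model specification is not the point here. But the article does fix 0.05 for all analyses and does promise a firm conclusion, so an SAP that added an adjustment would have to depart from that text.
- **Low prevalences are an unfavourable choice.** The list includes diabetes and hypertension requiring medication, which may be common. This stands: at 30% to 50% prevalence, power for an OR of 2 is 88% to 89%.
- **A compulsory Holm adjustment would worsen a harm it is meant to cure.** At its strictest step, power for an OR of 2 falls from 36% to 11% at 5% prevalence and from 59% to 26% at 10%, and exaggeration among the survivors grows. This stands, so adjustment is not required for an exploratory analysis.
- **The prevention phrase may refer to the conclusions as a whole.** This is possible; the item-level promise in the preceding sentence remains.

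A reader might infer that the study as planned runs a 43% risk of a false claim, or that a reported item has a 43% chance of being false. The documents support neither. The first holds only under the global null with independent tests. The second is a different quantity, which depends on how many items are truly related to POD and how strongly.

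**Conclusion.** The point holds as a mismatch between the strength of the promised conclusion and the rule that would produce it. An unadjusted 0.05 threshold across 11 items, in a study sized for one contrast, cannot demonstrate which items are independent risk factors. The chance of at least one false item is 43% at its upper limit, and about 23% to 42% under the more plausible scenarios of correlated tests (rho 0.1 to 0.5) or only 5 to 8 null items. All are several times the nominal 5%.

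How often true item effects would be missed or exaggerated cannot be settled from the article, because it depends on item prevalence. Uncommon items would be poorly served and common ones adequately served for an OR of 2.

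The matter is minor. The primary frailty–POD test keeps its 0.05 level, and neither the design nor the sample size is called into question.

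**What to change.** In Statistical methods, add that an item-level logistic model of POD will be fitted as an exploratory analysis, with all 11 mFI items entered together. State that all 11 ORs and 95% CIs will be reported whatever their p values.

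In the Discussion, replace *demonstrate* with *explore*, and say that no single item will be declared an independent risk factor or a prevention target on unadjusted p < 0.05 alone.

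A Holm-adjusted p value is optional. It is needed only if the authors wish to keep a confirmatory claim about individual items, and they should then accept the loss of power shown above.

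The cost is a few sentences and one results table. The downside is weaker item-level claims. Recruitment, data collection and the primary analysis do not change.

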### Trial status

This is the fourth version of the protocol. The first pre-screened participant was invited to be informed about the study on February 7th, 2022. The recruitment phase or the data collection phase of the trial will be completed by the end of December 2023 including post-test and one-year mortality measurements.

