### Participants

Patients with an ASA grade I–IV, age ≥ 70 years, and undergoing noncardiac surgery will be chosen from February 2022 to December 2023. The preoperative assessment will make use of the mFI and MMSE. Patients in the nonfrailty group will have a mFI < 0.21, and those in the frailty group will have a mFI ≥ 0.21. Enrollment will end once the projected sample size of patients in both groups has been reached.

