### Secondary outcomes

The incidence of 30-day readmission, one-year all-cause mortality, postoperative complications (such as pulmonary infection, urinary tract infection, cardiovascular and cerebrovascular accidents, abnormal liver function, postoperative bleeding, incision infection, lower extremity deep venous thrombosis, electrolyte disorder, and hypoproteinemia), and postoperative complications (such as infection of the incision, infection of the incision site, and postoperative bleeding) will all be considered secondary outcomes. According to the attending physicians’ definition, a hospital stay is the period of time between admission and discharge.

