### Participant timeline

On the day before surgery, candidates will be scrutinized according to the inclusion and exclusion criteria. According to their mFI scores, researchers will classify the participants into the frailty group or the nonfrailty group after receiving written informed consent. We’ll keep track of every intraoperative variable.

From the first to the third postoperative day, the patients will be checked on once in the morning and once in the afternoon, and the 3D-CAM score will be taken to gauge the frequency and seriousness of delirium. On the 30^th^ postoperative day, a phone follow-up will be finished, and any issues that develop within 30 days of the procedure will be noted.

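### Enrolment and one-year mortality follow-up share the same December 2023 end date, so no patient operated on in 2023 can complete one year on the stated schedule

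*Protocol article*

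**What the plan says.** Three statements in the protocol article set the calendar.

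- **Participants:** eligible patients "will be chosen from February 2022 to December 2023". The same section adds a stopping rule: "Enrollment will end once the projected sample size of patients in both groups has been reached".
- **Trial status:** "The first pre-screened participant was invited to be informed about the study on February 7th, 2022". The next sentence says that the recruitment or data collection phase will be "completed by the end of December 2023 including post-test and one-year mortality measurements".
- **Secondary outcomes:** the list begins "The incidence of 30-day readmission, one-year all-cause mortality, postoperative complications". One-year mortality is also in the title, the aims and the abstract.

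Two further statements bear on how the outcome would be obtained and analysed. The last contact described in the Participant timeline section is on day 30, when "a phone follow-up will be finished, and any issues that develop within 30 days of the procedure will be noted". Under Statistical methods, "Kaplan-Meier survival curves will be used to describe the incidence of secondary outcomes", with log-rank tests between the groups.

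**The concern.** A one-year outcome needs the end of follow-up to fall at least one year after the last operation. Here the last enrolment and the last mortality measurement fall in the same month. The word "or" in the Trial status sentence leaves unclear which phase is meant. Reading it as recruitment alone does not remove the conflict, because the sentence expressly puts the one-year mortality measurements inside the December 2023 completion.

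One-year mortality is one of the two outcomes in the title. If the stated close were followed, part of the cohort would be cut off before one year. The article does not say how large that part is or that it was intended. This is not detail that an article leaves to a fuller document, because the article gives both dates itself and they do not fit together.

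**Working it through.** **Inputs**

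- First participant approached 7 February 2022; close of data collection 31 December 2023 (Trial status).
- Recruitment February 2022 to December 2023 (Participants).
- Planned enrolment 536: 125 frail and 411 nonfrail (Sample size calculation).
- Even accrual over the window: an assumption, since the article gives no accrual rate.

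**Step 1. The plan's own sample size.** It is stated that "the incidence of POD in the frailty and nonfrailty groups was 35.7% and21.7"%, with a group ratio of 0.303, two-sided α 0.05 and power 0.80. The two-proportion formula with continuity correction gives 112 frail and 112/0.303 = 369.6, so 370 nonfrail. The total is 482, and 482/0.9 = 535.6, so 536. The stated figures reproduce. They concern delirium and do not depend on the follow-up dates.

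**Step 2. Latest operation date that allows a full year.** 31 December 2023 minus 365 days is 31 December 2022. Anyone operated on from 1 January 2023 reaches one year after the stated close.

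**Step 3. Share affected under even accrual.**

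- Window, 7 February 2022 to 31 December 2023, both days counted: 693 days.
- Part that allows a full year, 7 February to 31 December 2022: 328 days.
- Share able to complete one year: f = 328/693 = 0.473, and 536 × 0.473 ≈ 254 patients.
- Share unable: 1 − f = 0.527, or about 282 patients.
- By group, if accrual is even in each: 125 × 0.473 ≈ 59 frail and 411 × 0.473 ≈ 195 nonfrail patients could be observed to day 365.
- Starting the window on 1 February instead: 334/699 = 47.8% able, 52.2% unable.

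**Step 4. Other accrual patterns.**

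| Accrual pattern | Share unable to complete one year | Result |
|---|---|---|
| Declines linearly to zero | (1 − f)² = 0.527² | 28% |
| Even | 1 − f | 53% |
| Rises linearly from zero | 1 − f² = 1 − 0.473² | 78% |

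**Step 5. What the stopping rule would need.** Enrolling 536 over 693 days (about 22.8 months) is about 23.5 patients a month. Enrolling 536 by the end of 2022 (328 days, about 10.8 months) needs about 50 a month, with both group targets met. Stopping part-way through 2023 helps only in part. For example, even accrual ending on 30 June 2023 gives 181/(328 + 181) = 36% unable to complete one year.

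**Step 6. Cost to the planned Kaplan-Meier estimate.** Under even accrual, mean potential follow-up within the first year is 0.473 + 0.527 × 0.5 = 0.737 of a year, about 269 days. With a low, constant hazard (an assumption), the variance of the day-365 estimate rises by about −ln(0.473)/0.527 = 1.42 compared with complete follow-up. The standard error is then √1.42 = 1.19 times as large, equivalent to about 536/1.42 ≈ 377 patients fully followed.

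**The case against.** The strongest reply has four parts.

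1. **Censoring is already handled.** A reader might infer from the dates that one-year mortality cannot be delivered. The article does not support that. It plans Kaplan-Meier curves for secondary outcomes, and these accommodate administrative censoring. With some patients followed to day 365, survival at that point can be estimated. Counting 2023 patients as alive, or analysing only those with a full year, would do more harm, but the article proposes neither. This part stands. The loss is one of precision and of complete vital status.

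2. **The share lost is not known.** A reader might take it as fact that half the cohort is affected. That figure rests on even accrual. The article gives no accrual rate, and its stopping rule makes December 2023 possibly an outer limit. This stands as a limit on the size. It does not remove the conflict, because nothing in the article reports early closure and Trial status describes completion in the future tense.

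3. **The schedule may contain a one-year contact.** The Participant timeline text stops at day 30, and a reader might infer that no later contact is planned. Fig 1, which holds the assessment schedule, is not available in the text reviewed and may list one. The absence from the prose is supporting evidence at most.

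4. **It may be a drafting slip.** The Trial status sentence is loosely worded, and an intention to stop follow-up early is not established. That is plausible, but the stated date would still need correcting, since no section gives another.

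**Conclusion.** The point holds as an internal inconsistency between the Participants and Trial status sections. On the stated dates, no patient operated on in 2023 can complete one-year follow-up. That is about 53% of the cohort (about 282 of 536) under assumed even accrual, 28% to 78% across the linear accrual shapes tried, and none only if the stopping rule closed enrolment by the end of 2022.

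The consequence is confined to one secondary outcome, though it is one that the title names. Day-365 mortality would remain estimable, with a standard error about 19% larger under even accrual and a low constant hazard. That estimate also assumes that mortality risk does not change with calendar date of entry, since the later entrants are the ones censored. Complete one-year vital status for the whole cohort would not be available. Delirium and the sample size are untouched.

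**What to change.** Reconcile the two sections by stating two separate dates:

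- the date of last enrolment, actual or planned, saying whether the stopping rule applied;
- the end of mortality follow-up, set at the last patient's operation plus 365 days. That is December 2024 if enrolment runs to December 2023.

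Make sure the Participant timeline and Fig 1 both include a one-year vital-status check that records the date of death or the date last known alive. The Kaplan-Meier analysis needs these dates in any case. Do not lock the mortality data before the stated end of follow-up.

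If December 2023 is meant to stand as the close of data collection, the article should say that enrolment closed by the end of 2022, or else that later patients are administratively censored and how many they are.

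The cost is a change of wording, one vital-status check per patient that the outcome already requires, and a mortality report up to 12 months later. The delirium results can be reported on time.
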